As described, AI-C says that active inference is a necessary condition for a change in conscious perception. On a strong reading, this theory would be challenged if a stimulus can become consciously perceived in the absence of active inference. This basic active inference hypothesis relates to conscious content and what mechanism underpins a change from seeing something to seeing something else (or from seeing nothing to seeing something). A corollary of this minimal active inference theory relates to the fact that abolishing all active inference for a participant is very difficult or may be impossible without rendering them wholly unconscious. This is because active inference includes a very broad category of activity, essentially any policy-guided gain control (or precision control) anywhere in a system such as the human brain (noting that this leaves room for many types of activity that are not formally speaking policy-guided, such as interpretation, imagery, and generation of top-down predictions). The corollary specifies what the theory implies for cases where active inference is diminished to some degree but not abolished, leading to the hypothesis that with less active inference or less confident (i.e., precise) active inference, change in conscious content will be hindered, slowed down or prevented. This consequence of the theory is motivated by the precision of the beliefs over policies, where policies with precise expected outcomes will garner more evidence for the beliefs in question. For example, if a policy of passively fixating—i.e., suspending active inference—is contrasted with a policy of actively foveating to a specific target, then AI-C predicts with strong confidence that conscious content should be facilitated in the latter case. It is this consequence of AI-C that will be tested in the experiments described in this study protocol. The competing theories, NREP and IIT, make predictions in the same direction or predictions of no change, and with less confidence, since they do not stipulate policy-guided action as necessary for a change in consciousness, but acknowledge that action may change conscious experience.

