### Current study

Here, we describe a set of two experiments that form one of four Study Protocols (to be published separately), each of which is developed based on predictions of one of three major consciousness theories being tested in this adversarial collaboration (AI-C, IIT, and NREP).

As described above, the test of AI-C’s hypothesis proceeds by curtailing active inference in one, ‘passive’ condition, and contrasting that with an ‘active’ condition in which active inference leads to the selection of a policy of action with high expected information gain, with the prediction being that the active condition facilitates conscious awareness of the target. We will pursue this idea in a motion-induced blindness (MIB) paradigm, where a stationary peripheral target is rendered invisible due to the motion of a global pattern. We will contrast active sampling (via overt eye movement) with passive sampling (with eyes remaining at fixation) where, crucially, participants are exposed to identical visual input and retinal activation, and other task, attentional and expectation-related factors are kept constant. To assess the key prediction from AI-C that changes in conscious content will systematically occur earlier in the active condition, post hoc reports will assess whether the passively processed changes to sensory input are perceived later than the actively sampled changes.

In this study, we employ two experiments designed to assess these MIB active-passive differences (For more specific operationalised predictions relevant to the three theories considered in the adversarial collaboration (IIT, AI-C, NREP), see the section Operational Hypotheses below):

*Experiment A: Do changes in conscious experience occur earlier in the active than the passive condition?* This experiment will test whether the duration of MIB differs across the active and passive conditions. If there is no difference between conditions, or if MIB persists longer in the active condition, then that is strong evidence against AI-C. If MIB persists for longer in the passive condition, this would predominantly support AI-C.

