In Experiment A, participants will be excluded if they fail to report disappearances in more than 50% of trials or if they fail to generate a reappearance response in more than 25% of trials where they reported a disappearance. In Experiment B, participants will be excluded if they fail to reach the masking boundary at which there is stimulus reappearance <50% of the time, or in other words, if they fail to reach a threshold of stimulus awareness. Here ‘masking boundary’ describes a virtual circle, centred on the stimulus. If participants’ gaze enters this region, the stimulus will physically disappear. The same 50% rejection criteria will apply for reported disappearance and similarly participants who fail to complete > 25% of trials (including fixation, pre-cue period; post-cue period) for any reason will be excluded from data analysis. Furthermore, participants who do not meet the behavioural, eye tracking (e.g., microsaccade, eye-blink, and gaze location) exclusion criteria listed in the Data pre-processing section (below) will also be excluded from further analysis. Participant data collection will be considered complete when the total number of participants who surpassed these rejection criteria meets the stopping point defined above.

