*Main experiment*. Following the successful completion of training and practice trials, participants will be reminded (via diagram) how to complete active and passive trials before the main experiment begins. Participants will be informed that a cue in the active trial will allow them to move their eyes to look at the location where the target was previously seen; in contrast, in the passive trials the cue is an instruction to maintain fixation. During each experimental trial, the participant will be initially required to perform an uninterrupted fixation on a central dot for at least 1.5 seconds before responses can be given. If the participant is unable to maintain eye gaze on the target for more than 1.5 seconds, they will not be able to complete the trial. If the participant looks at the peripheral target stimulus during this time period, the trial will automatically end (and will not be counted as a valid trial). The participant will then be asked to press a button when the peripheral target stimulus entirely disappears; following this response, after a short delay (randomly jittered between 500ms-1000ms) a cue will be given to signal the next phase by flashing a different colour of the central fixation. In the active trial block, after the cue, the participant will be asked to look to the target location. In the passive block, participants will be told to maintain central fixation while the entire visual display (including the rotating grid) moves in relation to the fixation cross to eventually position, in an exact replay, the stimulus as it was in a randomly selected trial from the active block. Crucially, in this version of the experiment participants will be asked to respond as soon as they become aware of the target, thereby generating an estimate of the time to reappearance.

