Each trial will last a minimum of 4 seconds (1.5 seconds for fixation; 500 ms pre-cue delay; 2 seconds post-cue) and a maximum of 20 seconds, with a randomly selected inter-trial-interval (ITI) ranging 1.5–2 seconds (during which only a central fixation dot will be displayed). If the maximum trial time is reached—without all elements of the trial being completed—this trial will be removed from further analysis. Each condition will comprise 72 trials with a break every 24 trials (a trial block). In each block, two catch trials will be included; these will appear pseudo-randomly (excepting the first and last 3 trials) in each block and will involve the physical disappearance of the stimulus. Note that these catch trials will end as soon as the participant reports awareness of this disappearance. Blocks of active and passive trials will be interleaved such that 24 active trials will be followed by 24 replay trials until 144 (+12 catch trials) trials of each type have been shown. Each image will be shown a maximum of four times in the active trials. Accepted active replays will be carried across passive blocks but the angle of their movement trajectory towards the centre of the screen will be randomised. This will ensure that stimuli can be replayed in the passive block without leading to systematic confounds relating to a specific movement trajectory.

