**Fig 3 pone.0328836.g003:**
[figure not shown]
An example resolved LMM analysis decision tree for experiment A & B. Here solid lines denote variables to be considered and grey boxes (dotted lines) denote decision criteria. Note: 1) Crossed out options are for example only, all options are available in real analysis tree. 2) For display purposes only included variables are written in full but variable selection at each level includes the same forks. 3) The third level criteria uses ascending steps to decide model variable inclusion. 4) Top of the tree denotes the basic model.

Trials will be rejected if:

1)any button press response is made < 3 seconds following the start of the trial2)time to reappearance is reported < 250 ms following the cue.3)time to reappearance is reported > 1 second following the cue.

**2. Eye-tracking.** Binocular gaze and pupillary response data for the experiment will be sampled at a frequency of 1000 Hz using a desk mounted SR Research Eyelink 1000 system (35 mm lens). Testing will be conducted in a sound attenuated room and display luminance will be matched across recording sites (Melbourne and Jena) using luminance measures taken from the four screen quadrants, taking into account room lighting. Participants will be seated with their head stabilised on a chin rest mounted 105.3 cm from the stimulus presentation screen and ~55 cm from the eye-tracking camera to the eye. At the start of the experiment a nine-point calibration and nine-point validation will be conducted. An additional validation will be performed at the start of each block. If any inter-block validation is not considered ‘good’ (worst point error < 1.5°, average error < 1.0°), the initial calibration and block validation will be repeated.

***Passive condition, eye-movement replay.*** The replay data processing must be completed within the inter-block period and has therefore been kept relatively streamlined to prevent additional computation time:

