### Operational hypotheses

The hypotheses being tested by the experiments described in this Study Protocol are as follows:

Experiment A: changes in conscious experience manifest earlier in the active than the passive condition, as measured by behavioural responses;

Experiment B: backward masking can preclude changes in conscious experience in the passive condition but not (as much) in the active condition.

These hypotheses stem from the putative role of active inference to confirm the sensory input expected following action (as described in the Introduction). Active sampling should promote faster resolution of uncertainty, engendering earlier perceptual inference. These hypotheses can be expressed in terms of the following predictions about the patterns of data we expect to observe in each experiment:

1]*Subjective report of reappearance of peripheral stimuli will occur after a shorter delay following subjective disappearance in the active vs. the passive condition of Experiment A* (see Table 1).2]*The psychophysical reappearance threshold for the radius of the masking boundary (once eye gaze is inside this invisible circular boundary the stimulus is masked) will be higher ; i.e., a larger radius in the active vs. the passive condition of Experiment B* (see Table 2).

**Table 1 pone.0328836.t001:** Predictions about the effect of active (vs. passive) sampling on target time-to-reappearance in Experiment A.

Theory	Decrease	No change	Increase	Confidence
IIT	X	X		Low
NREP	X	X		Medium
AI	X			High

**Table 2 pone.0328836.t002:** Predictions about the effect of active (vs. passive) sampling on mask onset boundary distance in Experiment B.

Theory	Decrease	No change	Increase	Confidence
IIT		X	X	Low
NREP		X	X	Medium
AI			X	High

Each of the other theories considered in the adversarial collaboration, IIT and NREP, offer different predictions to these, which also differ in their degree of confidence:

IIT is consistent with both manipulations (active or passive target sampling) quickly breaking suppression, by changing visual cortex state. Motor involvement (active) may be enough to tip the balance towards breaking suppression more easily, for a small difference in time to reappearance and/or masking boundary. Thus, for Experiment A (see Table 1), IIT predicts either decrease or no change, with low confidence; for Experiment B (see Table 2), IIT predicts either increase or no change, with low confidence.

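### The 1-second upper limit on reappearance reports truncates the Experiment A outcome on the side where the passive condition is predicted to lie, and biases the active-passive difference toward zero

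*Protocol article*

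**What the plan says.** The trial rejection rules stand under Data collection procedures, 1. Behavioural Data. A trial is dropped if "time to reappearance is reported < 250 ms following the cue", and also if "time to reappearance is reported > 1 second following the cue". Only Experiment A has a timed reappearance report, so the upper limit matters there. Participants in that experiment "respond as soon as they become aware of the target, thereby generating an estimate of the time to reappearance", which makes the truncated variable the outcome itself.

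The predicted direction is explicit. Operational hypotheses, prediction 1, says that the report "will occur after a shorter delay following subjective disappearance in the active vs. the passive condition". The Introduction says that with less active inference "change in conscious content will be hindered, slowed down or prevented". The Experiment A design text adds that the target will eventually become visible in the passive condition too.

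The trial timing leaves room for later reports: "Each trial will last a minimum of 4 seconds (1.5 seconds for fixation; 500 ms pre-cue delay; 2 seconds post-cue", with a maximum of 20 seconds per trial. Under Current study, the consequence of a null is fixed: "If there is no difference between conditions, or if MIB persists longer in the active condition, then that is strong evidence against AI-C". Participants are excluded "if they fail to generate a reappearance response in more than 25% of trials where they reported a disappearance".

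The article gives no reason for the 1-second value and describes no analysis without it.

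**The concern.** A response-time limit set in advance is not wrong in itself. The difficulty is where this one sits: on the outcome, inside the response period, and on the side where one condition is predicted to lie. Late passive reports are the signal the theory predicts, and the rule deletes them. The rule is worded identically for both conditions, but its effect is not identical once their distributions differ.

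What is at stake is the comparison of theories. Table 1 allows IIT and NREP to predict no change and does not allow it for AI-C. A rule that pulls the difference toward zero therefore works against one of the three theories in a study meant to weigh them evenly. The protocol fixes the rule itself, so this is not a detail left to an analysis plan.

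**Working it through.** **Inputs from the article.** Limits of 250 ms and 1 s after the cue; post-cue period of at least 2 s; 55 participants for at least 80% power at partial eta squared 0.13.

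**The article's own figure.** f² = 0.13/0.87 = 0.149. For a paired contrast with n = 55, the noncentrality is 0.149 × 55 = 8.2. The noncentral F(1, 54) at two-sided alpha 0.05 (assumed) gives 80.4% power; n = 54 gives 79.6%. The 55 reproduces. It serves only as the 80% baseline for the power check below.

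**Assumptions.** The article gives no mean, SD or shape for report times. I assume log-normal cue-to-report times with log-SD σ = 0.30, an active median of 450-850 ms and a true mean passive delay of 100 ms.

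**Formula.** For a log-normal with log-median μ kept between a and b, the mean is exp(μ + σ²/2) × [Φ(z_b − σ) − Φ(z_a − σ)] / [Φ(z_b) − Φ(z_a)], with z_x = (ln x − μ)/σ. The share lost above 1 s is 1 − Φ(z_1), where z_1 = −μ/σ.

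**Worked case: active median 650 ms, proportional delay.**
- Active: full mean 0.65 × exp(0.045) = 0.680 s. z_1 = 1.436, so 7.6% exceed 1 s. Mean after both limits: 0.680 × 0.8718/0.9238 = 0.642 s.
- Passive: every time multiplied by 1 + 0.1/0.680 = 1.147, full mean 0.780 s. z_1 = 0.979, so 16.4% exceed 1 s. Mean after both limits: 0.780 × 0.7513/0.8360 = 0.701 s.
- Observed difference: about 59 ms of a true 100 ms.

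**Three kinds of delay** (simulation, 2 million draws each, both limits applied; share of the true 100 ms that remains):

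| Active median | Constant shift | Proportional | A quarter of passive trials delayed, exponential with mean 400 ms |
|---|---|---|---|
| 450 ms | 91% | 86% | 37% |
| 650 ms | 77% | 59% | 18% |
| 850 ms | 55% | 34% | 9% |

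At 650 ms the upper limit removes about 7.6% of active and 14-18% of passive trials. At 850 ms it removes about 29% and 39-43%. With the upper limit at 2 s instead, 71-100% of the difference remains over the same grid. At 450 ms part of the loss comes from the 250 ms floor: for the constant shift, 94% remains with a 2 s limit against 91% with 1 s.

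**Other shapes.** Ex-Gaussian and further log-normal distributions (active mean 500-900 ms, delay 50-200 ms) leave 28-98% under the 1 s limit alone and 28-95% with both limits. In every scenario more passive than active trials exceeded 1 s and the mean difference shrank.

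**Power.** Participant-level simulation (ex-Gaussian times, 55 participants, 72 trials per condition, calibrated to 80% before truncation) gave 85-99% at active means of 500-600 ms, 46-82% at 700 ms and about 5-70% at 800-900 ms. Trimming also removes noise, so power can rise while the difference shrinks.

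**The case against.** The strongest reply is that the size is assumed. With an active median near 450 ms and a uniform slowing, 86-91% of the difference survives. The low figures need slow medians, at which the rule would discard over a quarter of active trials, and completed piloting would probably have shown that. This stands as a limit on size. It does not change the direction.

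Some stronger readings are tempting and are not supported:
- **The effect is nearly erased.** This holds only when the delay affects a fraction of passive trials and is long-tailed or the median is slow. With a fixed 400 ms delay in a quarter of trials, about half remains at a 550 ms median and 31% at 650 ms.
- **The rule produces a null result or costs power.** A smaller mean difference is neither. Power held or rose in the faster scenarios. The planned generalized linear model may also not use the raw mean difference computed here.
- **Late reports count toward the 25% exclusion.** That criterion concerns failure to generate a response, and a report after 1 s is a generated response. The article does not say otherwise, though a clarifying sentence would help.
- **Two seconds is the response deadline.** It is a component of the minimum trial length. No fixed post-cue deadline is stated, so no single censoring time can be read from the text.

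The rule also creates no difference where the two distributions are equal.

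**Conclusion.** The concern holds on direction. If passive reappearance is slower, the rule deletes more passive than active trials and biases the mean difference toward zero, against the one theory for which the article treats no difference as strong contrary evidence. That follows from the stated rule and prediction. The size does not: over the assumed log-normal grid the retained share runs from 9% to 91%, depending on the median and on whether the delay affects all passive trials or only some. If nearly all reports fall well under 1 second, the loss is a few percent. The finding is bias in the estimated difference, not a general loss of power and not a predicted null.

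**What to change.** Record a timestamped amendment before results are seen:

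1. Remove the 1-second upper limit from the primary Experiment A analysis. Keep all reports of at least 250 ms up to the end of the trial's response period, with a model suited to right-skewed times. Planned analyses already leaves the link function to the distribution of the data, so no new model family has to be imposed.
2. Report the numbers of rejected and no-report trials by condition.
3. Give the 1-second version as a sensitivity analysis. Add a time-to-event analysis that censors no-report trials at the recorded end of each trial. It assumes that a missing report means the target stayed invisible and not a lapse, so it belongs among the sensitivity analyses.
4. Keep the 25% no-response exclusion, and state that a report later than 1 second counts as a response.

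Cost: no new data, but agreement is needed from both sites and the three theory leads while data collection is underway. Some slow lapses will stay in the data and add variance, which the 1-second sensitivity analysis will help to show.

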## Materials and methods

### Aim

The aim of this study is to contrast passive and active conditions using peripheral targets in MIB. In the active condition—after the participant reports the initial disappearance (fading from awareness) of the stimulus—they will be cued to saccade to the previously observed location of the target. This saccade is considered as a manifestation of overt active inference. In the passive condition, following a reported disappearance, the sensory consequences of the saccade are ‘replayed’ by moving the stimulus array (which includes the grid), while central fixation is maintained. Passive replay will be based on eye movement trajectories recorded via eye tracking during the active condition, thereby ensuring that visual stimulation is identical across conditions. In each condition, participants will be instructed to indicate—via button press—when the target reappears in consciousness (see Fig 1).

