1)Replay periods are epoched using a window extending from the initialization of the cue to the first fixation on the target stimulus.2)Any values outside of the boundaries of the screen are removed, and eyeblink periods must be linearly interpolated between points in order to maintain a smooth replay. Any datapoint more than 1.5° of visual angle away from the linear path from fixation to target will not be considered in the replay. Any datapoint more than 1.5° away from the previous data point is considered an error and will not be considered in the replay.3)Any trials containing poor signals (i.e., missing more than 20% of sample points in both eyes; [41]) will not be selected for replay. For replays that meet this standard all non-included samples will be linearly interpolated. To ensure equal numbers of active and passive trials, active trials may be used in replays additional times after running through all available replays. The replay path corresponding with the target stimuli will be used for replay if available, but the path trajectory will be transformed across randomly selected polar angles.

***Analysis.*** The following pre-processing steps describe the post-experiment analysis of eye tracking data for use in trial validation, eye-blink, microsaccade and pupillometry measures:

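### The listed replay steps do not remove a constant eye-tracker offset within the accepted calibration error, and the end point of the passive replay is unclear, so identical retinal input across conditions is not secured

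*Protocol article*

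**What the plan says.** The protocol article commits to sameness of input in three places. Under Current study it says that "participants are exposed to identical visual input and retinal activation". Under Aim it says the replay is built from recorded eye movements, "thereby ensuring that visual stimulation is identical across conditions". The Main experiment text for Experiment A has the display moved to place, "in an exact replay, the stimulus as it was in a randomly selected trial from the active block".

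Under Data collection procedures, item 2 (Eye-tracking), calibration is repeated only when a block's validation fails the limits "worst point error < 1.5°, average error < 1.0" degrees. Validation takes place at the start of each block.

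The subsection on the passive condition's eye-movement replay lists the processing. The first step is "Replay periods are epoched using a window extending from the initialization of the cue to the first fixation on the target stimulus". Off-screen samples are removed and blinks interpolated. Two distance filters follow: "Any datapoint more than 1.5° of visual angle away from the linear path from fixation to target will not be considered in the replay", and "Any datapoint more than 1.5° away from the previous data point is considered an error and will not be considered in the replay". Trials missing more than 20% of samples are not replayed, and paths are rotated to random polar angles. No step aligns the start or end of the path or subtracts an offset.

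Other sentences describe the end point differently. The Experiment A design text has the passive target brought to central fixation and held there, and the paragraph on trial numbers speaks of a trajectory towards the centre of the screen.

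**The concern.** Recorded gaze is true gaze plus tracker error. In an active trial the error does not affect what the participant sees: the eye is where it is, and the target falls on the retina at the true landing offset. In a passive trial the recording is the stimulus. If it is replayed as recorded, a constant tracker error becomes a physical shift of the target relative to a viewer who holds fixation. The error then enters one condition only.

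Current study treats a null result in Experiment A as strong evidence against AI-C, and longer blindness in the passive condition as predominantly supporting it. A retinal difference between conditions that has nothing to do with action could therefore affect which theory the result is read as favouring. The covariates and measures named under Planned analyses and expected outcomes (inter-beat interval, time-on-task, microsaccades, pupil) do not include gaze-to-target distance, so the named analyses would not show it.

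**Working it through.** The plan gives no figure for replay fidelity, so there is none to reproduce. The relevant figures are the validation limits (1.0° average, 1.5° worst point), the 9° target eccentricity, the 105.3 cm viewing distance and the 1000 Hz sampling rate.

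**1. Scale.** At 105.3 cm, 1.0° is 105.3 × tan(1.0°) = 1.84 cm and 1.5° is 2.76 cm, or 11% and 17% of the 9° path. Validation covers the start of a block only. With 24 trials plus 2 catch trials, a block lasts roughly 26 × (4 + 1.5) s = 2.4 min to 26 × (20 + 2) s = 9.5 min.

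**2. Do the listed steps remove a constant offset?**
- Path filter: it drops samples more than 1.5° to the side of the line. An error under 1.5° has a sideways component under 1.5°, so taken alone it passes. Error along the line is not tested.
- Jump filter: 1.5° between samples 1 ms apart is 1,500° per second. This catches spikes. A constant offset produces no jump between samples.
- Rotation: it changes the direction of the offset and keeps its length.

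**3. Reading A: the replay ends at the recorded gaze point.** Let L be the true landing offset, normal with SD s on each axis, and e the tracker error in a random direction. The active distance is |L| and the passive distance is |L + e|. Neither s nor e is in the document. I assumed s = 0.4, 0.6 and 0.8°, and replays accepted when |L + e| is at most 1.5°, at most 2.0°, or without limit. There were 400,000 draws per scenario, with both conditions compared on the same accepted trials.

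| Tracker error e | Mean added passive distance | Trials with passive farther |
|---|---|---|
| 0.25° | 0.01–0.05° | 53–62% |
| 0.5° | 0.04–0.18° | 56–73% |
| 1.0° | 0.13–0.58° | 59–89% |

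Example with s = 0.6°, e = 1.0° and no limit: the active mean is s × √(π/2) = 0.75°, the passive mean is 1.20°, and the difference is 0.45°.

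**4. Sensitivity to the comparison set.** The article's rules for selecting replays (20% missing, path filters) differ from its rules for analysed trials (30% missing, target fixated). Comparing accepted replays with all active trials can reverse the sign. With s = 0.8° and a 1.5° limit, the passive target is nearer by 0.17° (e = 0.25°), 0.15° (0.5°) and 0.07° (1.0°).

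**5. Reading B: the replay ends at screen centre.** The passive distance is then 0 and the active mean is s × √(π/2): 0.50°, 0.75° and 1.00° for s = 0.4, 0.6 and 0.8°. The passive target is the better centred one by those amounts.

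**6. Experiment B.** A constant error e in a random direction shifts the true distance at which the mask fires by e/√2 RMS along the path, about 0.7° for e = 1.0°.

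**The case against.** The strongest objection is that the article itself speaks of the passive target being brought to central fixation. If the path is snapped there, no tracker error remains at the end point. That is correct, but it then contradicts the promised replay of an active trial, and step 5 shows the retinal input still differs, in the other direction.

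A second objection is that a condensed article may omit offset handling that exists in the code. That is possible. However, the replay steps are enumerated with numerical thresholds and described as deliberately streamlined, and those steps do not deliver the identity claimed for them.

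A third is that 1.0° and 1.5° are acceptance ceilings. This stands: achieved error is not reported, and at 0.25° the added displacement is negligible.

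A reader might infer that tracker error throws the passive target off the fovea and always favours the active condition. The document does not support this:
- The face is 200 × 200 pixels, which is about 2.2–4.4° wide at an assumed pixel pitch of 0.020–0.040 cm, so a 1.0° shift normally leaves fixation on the face, off-centre.
- The direction varies from trial to trial, and the mean can change sign with the comparison set.
- An offset at the start of the path could make the display jump at the cue and break suppression sooner in the passive condition.
- Reappearance may be reported before the movement ends, so final centring need not drive the response time.

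**Conclusion.** The point holds as a gap between the claim and the procedure. Following the listed steps does not secure identical retinal input, whichever end point is meant. If the recorded end point is used, the passive target is on average 0.01–0.05°, 0.04–0.18° or 0.13–0.58° farther from the fovea for tracker errors of 0.25°, 0.5° and 1.0°. If it is snapped to centre, the passive target is 0.50–1.00° nearer.

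These figures rest on assumed landing scatter of 0.4–0.8° per axis, randomly directed error and, for the first set, assumed acceptance limits with both conditions compared on the same accepted trials. The tracker errors are assumptions at or below the ceiling for average error, not measured performance. The document gives no milliseconds per degree, so neither the direction nor the size of a bias in reappearance time can be stated. The gap calls for correction and reporting; it does not show that the Experiment A contrast is biased towards any theory.

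**What to change.** 1. **Replay, remaining sessions.** Before the two 1.5° checks, subtract from each trial's gaze path the median offset from the dot during the central fixation already required (at least 1.5 s per trial, at a known position). Use the same corrected gaze to trigger the Experiment B boundary. State whether the replay ends at the recorded landing point or at screen centre, and reconcile the Experiment A design and trial-number text with the Main experiment and replay text.
2. **Analysis, all data including those already collected.** Compute the corrected gaze-to-target distance at the end of the movement for every active and passive trial and report it by condition. Add a sensitivity analysis restricted to a common distance limit in both conditions, or adjusted for distance.

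Central-fixation correction removes only the constant part of the error. Error specific to the target location 9° away may remain in the recording.

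The cost is a few lines of code and a dated amendment, because collection is under way and the article already describes an amendment route. No extra participants are needed. The downside is a replay step that differs between earlier and later sessions, so results should identify which version each session used. Tighter calibration limits are not needed for this fix; the document gives no basis for choosing any.
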